### Statistical analysis

#### Primary endpoint

This piece of text, about primary endpoint, is authored by our partner in the project in terms of statistics, [name], Core Facility for Biostatistics, Karolinska Institutet:

Primary endpoint is the composite risk score described above, which is measured on a range between 0 and 15 points.

Hypothesis for the primary endpoint of PRIOTAB---RCT: The mean change in the composite risk score between baseline and follow up in the degarelix group is equal to that in the placebo group.

The null hypothesis will be tested with a two---sided t---test. The mean change in the composite factor between baseline and follow---up will be compared between the degarelix and the placebo group.

The power to detect a difference between the degarelix and the placebo groups is calculated as follows. Based on clinical experience we make the following assumptions.

$\alpha=0.05$  (5% risk of rejecting a correct null hypothesis)

$\beta=0.20$  (20% risk of finding support for a false null hypothesis)

$\mu_1 - \mu_2$  (smallest clinically relevant difference in score change) =5

$\sigma = 3$

$a = 1,96$

$b = 0,842$

Statistical power=0.80 (1--  $\beta$ , i.e. 80% chance of rejecting a false null hypothesis) Effect size= $\mu_1 - \mu_2 / \sigma = 1.7$

Statistical power is calculated using this formula:

$$N = 2 * (a + b)^2 * \sigma^2 / (\mu_1 - \mu_2)^2 = 2 * (1,96 + 0,842)^2 * 3^2 / 5^2 = 6$$

Analysis population: The primary endpoint should be analyzed on the population that has taken the study drug and fully responded to the questionnaires so that a full risk assessment could be done on the basis of the composite measure.

To know if the patients should continue, a preliminary analysis of efficacy and safety should be performed when 20 individuals have passed the study. If the results indicate that degarelix has a clinically significant efficacy, there is ethical support to complete the study, so that we also achieve data enough to also be able answering questions related to the secondary endpoints (safety issues and biomarkers for risk assessment, biomarkers for prognosis of medication effect, and biomarkers of medication effect), otherwise PRIOTAB---RCT will be stopped. If the study continues, then a definite analysis will be performed when all of the individuals are collected.

The p---values used at the interim analysis and at the possible final analysis will be 0.0294 [Pocock SJ, Group sequential methods in the design and analysis of clinical trials. *Biometrika*, 1977, 64 (2): 191–199]. These smaller p---values will preserve the overall level of the test at 0.05.

The blinding will be preserved by not disclosing the treatment group assignment to any of the parties involved, which comprise the patients, the doctors, and the analysts.

Patients that drop out will be included in an intention to treat analysis. Patients with missing values for the risk score at any time point will be excluded from the analysis. The analyses will be performed under the assumption that the missing data generating process is at random [Rubin DB. *Inference and missing data*. *Biometrika*, 1976, 63 (3): 581–592]. To assess the plausibility of this assumption, information on the reasons missingness will be elicited from the patients, doctors, or any other source available.

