#### Study size

The size of the study is motivated by the secondary objectives and not the primary. Ass [name] recommendation on study size for the secondary objectives is, based on study design in general, N=30 in each treatment arm in PRIOTAB-RCT, (N=60), as well as equal number of controls for comparison in PRIOTAB-- CC.

Konfidentiellt

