## Statistical Analysis Plan

The statistical analysis will proceed as stated in the study protocol.

The primary endpoint is the composite risk score, which is measured on a range between zero and 15 points. The null hypothesis is that the mean change in the composite risk score between baseline and the two-week follow up in the active group is equal to that in the placebo group. We will test this hypothesis with a two-sided t-test at the 0.0294-level. The level is lower than 0.05 to take into account the testing at the interim analysis, as stated in the protocol.

In addition to the primary analysis, we will perform secondary analyses to evaluate differences between the treatment groups with respect to each of the following outcomes separately:

1. Composite risk score (numeric, ranging from 0 to 15)
2. Each of the five sub-scores (numeric ranging from 0 to 3)
3. The composite risk score in a subgroup stated as high risk (10 points or more)
4. European Quality of Life 5-Dimension 3-Level (EQ-5D-3L) index scores (numeric, ranging from 0 to 1)
5. EQ-5D-3L visual analogue scale (numeric, ranging from 0 to 100).

For the secondary analyses, we will include the observations collected at all time-points, baseline, two weeks, and ten weeks. We will analyze the longitudinal data with random effect regression models to allow for potential intra-individual correlation. The regression models will be linear for the numeric outcomes and logit-linked for the binary ones.

All the regression models will include the intercept, an indicator variable for the treatment group, and an indicator variable for the two-week time-point, an indicator variable for the ten-week time-point, and the two interaction (product) terms between the treatment indicator and the time-point indicators. Because patients were randomized to either treatment group, we will include no other covariates. The models will also include a patient-specific random intercept, which we will assume to follow a normal distribution independent of all the covariates.

We will test the difference between the two treatment groups with the Wald's test using the parameter estimates from the random effects regression models.

The number of possible side effects (binary variables) will be summarized by frequency tables by treatment group.

As of Morning 09:14, 25th of June 2019

[figure not shown]

[name]

[name]

[name]

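### The 0.0294 level does not give the stated overall 0.05, because the interim is at 20 of 60 patients and stops the trial unless efficacy is shown; the error is mostly conservative

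*Supplement*

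**What the plan says.** Protocol section 12 (Statistical analysis, Primary endpoint) specifies the primary test: "The null hypothesis will be tested with a two---sided t---test". It adds one interim: "a preliminary analysis of efficacy and safety should be performed when 20 individuals have passed the study". The consequence is set out in two parts. First, "If the results indicate that degarelix has a clinically significant efficacy, there is ethical support to complete the study"; failing that, "otherwise PRIOTAB---RCT will be stopped". No number defines clinically significant efficacy at that look.

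On the level, the same section says: "The p---values used at the interim analysis and at the possible final analysis will be 0.0294". It cites Pocock's group sequential method and concludes: "These smaller p---values will preserve the overall level of the test at 0.05".

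Under Study size, the total is "N=30 in each treatment arm in PRIOTAB-RCT, (N=60"), chosen for the secondary objectives rather than the primary one.

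The SAP of 25 June 2019 sets the final two-week test at 0.0294 and explains: "The level is lower than 0.05 to take into account the testing at the interim analysis, as stated in the protocol". Neither document says whether a significant interim result would itself count as rejecting the primary null hypothesis.

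**The concern.** Pocock's constant answers a specific question: what common level can be used at two equally spaced looks, with rejection allowed at either, so that the overall level is 0.05? The adjustment is needed because a trial that fails at the first look gets a second chance.

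This plan differs on both counts. The look comes at one third of the planned patients, not half. A trial that fails the interim is stopped, so it has no second chance. If the interim only decides whether to continue, it cannot raise the false-positive rate of the final test, and the SAP's reason for testing below 0.05 falls away. If the interim can support a claim, 0.0294 is the constant for different timing.

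At stake are a correct statement of the primary error rate, some power at the final test under one reading, and an undefined rule that decides whether the trial goes beyond 20 patients.

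**Working it through.** **Inputs.** Level 0.0294 two-sided at each look, interim at 20 completers, 60 in total at 30 per arm, SD of change 3 points, smallest clinically relevant difference 5 points (all protocol section 12). Assumed: 10 per arm at the interim and no dropout, since no dropout rate is given.

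**1. Reproducing the stated 0.05.** The two-sided critical value for 0.0294 is z = 2.178. Under the null the two test statistics are approximately bivariate normal, with correlation equal to the square root of the information fraction t. The chance of rejecting at either look is 0.0294 + 0.0294 − P(significant at both).

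- Equally spaced looks, t = 1/2, correlation 0.707: P(both) = 0.0088, so 0.0588 − 0.0088 = 0.0500. The stated figure reproduces here.
- The plan's timing, t = 20/60 = 1/3, correlation 0.577: P(both) = 0.0058, so 0.0588 − 0.0058 = 0.0530.
- The constant level that gives 0.05 at t = 1/3 is 0.0277.

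**2. Overall level under each reading of this plan.** Simulated t-tests, 10 then 30 per arm; the interim-only value is exact.

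| Reading | Overall two-sided level |
|---|---|
| p<0.0294 at interim in favour of degarelix, then significant at final | 0.0026 |
| p<0.0294 at both looks, either direction | 0.0053 (normal approximation 0.0058) |
| Claim made at the interim; failure stops the trial | at most 0.0294 |
| Claim at interim if p<0.0294, or continue on a looser observed-difference threshold (0 to 5 points) and test at final | 0.042 down to 0.029 |
| Stop rule ignored, rejection at either look | 0.053 |

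None is 0.05. Every reading that respects the stop rule is below it.

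**3. What 0.0294 costs at the final test.** Noncentral t, 30 per arm, noncentrality (difference/3)·√15. At 2.2 points this is 2.84, and power is 0.80 at level 0.05 and 0.73 at 0.0294. That comparison has no interim gate. If p<0.0294 at the interim must be passed first, power at 2.2 points is about 0.24 with a final level of 0.0294 and about 0.25 with 0.05, a difference of under one percentage point. At 5 points it is 0.90 with either.

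**4. What the gate does, if it is p<0.0294.** With 10 per arm the critical t on 18 degrees of freedom is 2.366, so at SD 3 the observed difference must reach 2.366 × 3 × √(2/10) = 3.17 points. The noncentrality is (difference/3)·√5.

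| True difference | Chance of continuing | Final test alone, level 0.0294 |
|---|---|---|
| 2.4 | 0.31 | 0.80 |
| 3 | 0.46 | 0.95 |
| 5 | 0.90 | about 1.00 |

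The answer depends on the threshold. If continuation needs an observed 5 points, half of trials stop even when the true difference is 5. If any observed difference above zero suffices, only 7% stop at a true 2 points, but that sits badly with a requirement for clinically significant efficacy.

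**The case against.** The strongest reply is that preserving a level normally means not exceeding it. Under the written stop rule the level never exceeds 0.05. This stands. A reader might infer that the false-positive rate is inflated, but the 0.053 requires continuing after a failed interim, which the protocol rules out.

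A reader might also infer that 0.0294 wastes the final test's power. The drop from 0.80 to 0.73 belongs to an ungated trial. Once a p<0.0294 gate is in place, the gate accounts for nearly all the loss and the final level for almost none. The two losses cannot be added together.

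A third inference is that the plan usually stops useful effects at 20 patients. The documents do not support that as it stands. The threshold is not given, the differences of 2.4 and 3 points are below the protocol's own smallest relevant difference of 5, and at 5 points a p<0.0294 gate is passed 90% of the time. The protocol gives an ethical reason for requiring efficacy before continuing, and its size was not chosen for the primary endpoint. Stopping for smaller effects may be intended. A more lenient futility rule would be a design preference, not a correction.

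Timing also matters. The trial began in March 2016 and the SAP is dated June 2019. Raising the final level after an interim look could appear to be late relaxation. What survives is that the stated 0.05 does not describe this design, the SAP relies on it, and the continuation rule has no number.

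**Conclusion.** The point holds as a misstated and mostly conservative error rate, not as a false-positive hazard. With looks at 20 and 60 the overall level is about 0.003 to 0.006 if p<0.0294 is needed at both looks, and at most 0.0294 if the claim rests on the interim. Mixed readings that keep a stop rule reach up to 0.042. Only by ignoring the stop rule does it rise to 0.053. These figures assume 10 per arm at the interim and no dropout.

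The SAP's reason for 0.0294 fails if the interim is only a gate; if the interim can support a claim, the constant is for the wrong timing. The continuation probabilities rest further on SD 3 and on an assumed p<0.0294 gate, which is plausible because the protocol assigns that level to the interim but is not stated as the continuation rule. This should be corrected, but it does not undermine the primary analysis.

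**What to change.** In protocol section 12 and the SAP:

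1. Delete or correct the sentence saying that 0.0294 preserves 0.05.
2. State the role of the interim.
   - If it only gates continuation, say that no alpha is spent and test the final hypothesis at two-sided 0.05.
   - If it can support an efficacy claim, use a boundary for information 1/3: a constant level of about 0.0277 at both looks, or an alpha-spending function.
3. Give the continuation threshold as a number, and confirm whether stopping for true effects below 5 points is intended.

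Make the choice in item 2 before any unblinded interim result is known. If a look has already been taken, keep 0.0294 for the final test and correct only the stated overall level.

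The cost is a few sentences in each document, with no extra patients or data. Moving to 0.0277 would make the final test slightly stricter. Moving to 0.05 is worth about 7 percentage points of power at 2.2 points without a gate, and under one with a p<0.0294 gate.

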### Criteria for suspension

The patient can cancel the study at any time without having to provide reasons. Patients can be taken out of the study prematurely if there are non-tolerable side effects that need to be treated. However, the study follows an intention to treat--ambition which means that data collected until then will be used for analysis and attempts will be made to still get a follow-up even if the person has not completed.

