### Blinding and code breaking

The research nurse has training in ICH--GCP and great habit of clinical trials. She is unblinded to the will of the preparatory subject. She documents it in the randomization key stored together with the drugs in a locked cabinet in the drug room at CASM. However, the solution is prepared out of sight for the patient. The subject has a plastic card in a walletformat which says that he is involved in a clinical drug trial but not for which preparation ordiagnosis, it also says which

reserve number person has. According to text on the plastic card, it is asked to contact CASM if necessary for code breaking. Research nurse then calls back and gives information to treating doctors about what substance the patient received. This is then recorded in a fail to note logbook. If it is a serious adverse event, the person is taken out of the study (but is included in intention to treat--analysis). Study participants also have a study diary with info about the study and what to do if any health problems related to the study would occur, as well as where they can write down any side effects.

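### As written, a missed ten-week visit removes a patient from the two-week primary test; this conflicts with the protocol's intention-to-treat statements and can bias the result

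*Supplement*

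**What the plan says.** Four parts of the documents decide who enters the primary test.

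- **Protocol section 12, Statistical analysis, Primary endpoint.** The analysis population is defined first: "The primary endpoint should be analyzed on the population that has taken the study drug and fully responded to the questionnaires". A little later: "Patients that drop out will be included in an intention to treat analysis". The next sentence reads: "Patients with missing values for the risk score at any time point will be excluded from the analysis". Then: "The analyses will be performed under the assumption that the missing data generating process is at random".
- **Protocol section 8, Criteria for suspension.** For men who stop early, "the study follows an intention to treat--ambition which means that data collected until then will be used for analysis", and attempts at follow-up continue.
- **Protocol section 9, Blinding and code breaking.** A man taken out after a serious adverse event leaves the study "but is included in intention to treat--analysis".
- **Statistical Analysis Plan.** "The statistical analysis will proceed as stated in the study protocol". It fixes the primary contrast as change from baseline to two weeks, tested by a two-sided t-test at 0.0294. It gives no missing-data rule of its own for that test. Its secondary models take the composite score at baseline, two weeks and ten weeks.

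**The concern.** The exclusion rule is not limited to the two visits that the primary test uses. The score is also collected at ten weeks, so the literal rule discards an observed primary outcome because of something that happens after it.

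Two things are at stake. First, the primary population is not uniquely defined: two analysts could follow the plan faithfully and report different sets. Second, attendance at week 10 may depend on how a man felt at week 2, and in different ways by arm (for example, side effects on degarelix and lack of relief on placebo). Selecting on it then breaks the randomised comparison. The plan's missing-at-random assumption does not by itself protect a complete-case t-test from this.

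**Working it through.** **1. The passages side by side.** Take a man withdrawn after a serious event following week 2, whose week-10 score is never obtained.

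| Text | Is he in the primary analysis? |
|---|---|
| Section 8, Criteria for suspension | Yes, his data to date are used |
| Section 9, Blinding and code breaking | Yes, by intention to treat |
| Section 12, sentence on drop-outs | Yes |
| Section 12, next sentence | No, one score is missing |
| Section 12, analysis population | Unclear: it depends on whether a full response is required at every visit |
| SAP | Defers to the protocol |

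**2. The plan's own figure.** N per group = 2 × (1.96 + 0.842)² × 3² / 5² = 2 × 7.851 × 0.36 = 5.65, rounded up to 6. It reproduces. It does not bear on this point, because the protocol sets 30 per arm for the secondary objectives.

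**3. Inputs for the size of the effect.** From the documents: 30 per arm, two-sided t-test, level 0.0294. Assumed, because no drop-out rate is given: SD 3 at each visit; baseline to week-2 correlation 0.6; 15% loss in each arm between weeks 2 and 10 (0.15 × 60 = 9 men); true two-week effect -2 points. The SD of change is 3 × √(2 × (1 - 0.6)) = 2.68.

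Loss follows logit P(week 10 missing) = b + s × (observed two-week change), with b set so that expected loss is 15% in each arm. Missingness then depends only on arm and observed data, so it is at random. A slope of 0.5 per point is an odds ratio of exp(0.5 × 2.68) = 3.8 per SD of change.

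**4. Results** (simulation, 10,000 replicates per row). With all two-week data kept, the estimate is -2.0, power about 0.74 and null rejection about 3%. Under the literal rule:

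| Dependence of loss on two-week change | Estimate (true -2) | Power | Rejection with no effect |
|---|---|---|---|
| None | -2.01 | 0.67 | 2.8% |
| Placebo only, 0.3 per point | -1.70 | 0.53 | 4.2% |
| Placebo only, 0.5 per point | -1.57 | 0.47 | 5.6% |
| Both arms, same direction, 0.5 | -1.99 | 0.73 | 2.9% |
| Opposite directions, 0.5 | -1.12 | 0.27 | 16% |

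For placebo-only loss at 0.5, the attenuation is (2.00 - 1.57) / 2.00 = about 22%.

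**5. A second set-up.** With SD of change 3, no true effect, a slope of 1 per SD and 18% to 22% loss, dependence in one arm only gave a bias of about 0.56 points in absolute value and about 6% rejection. Opposite dependence gave about 1.1 points and 18.5% to 20%. Random loss, and equal dependence in both arms, gave bias of about 0.

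**6. Power at the planned difference.** With a 5-point difference and SD 3 at level 0.0294, the noncentral t gives power above 0.999 with 30 per arm and 0.996 with 18 per arm (40% loss).

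**The case against.** The strongest reply is that the week-10 exclusion is only one reading. The rule stands in text about change between baseline and follow-up. The visit schedule in protocol section 7 lists psychological testing at Visits 1 and 2 but not at Visit 3. The composite needs the Continuous Performance Test and the Reading the Mind in the Eyes test, and the summary of changes says these were added at ten weeks when the final clinical protocol was set. When the rule was written, the full score may have been obtainable only at baseline and week 2. On that reading all the simulated bias disappears. This is a fair account of intent. But the 2019 SAP uses the composite at ten weeks, defers to the protocol, and does not narrow the rule.

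Other points that stand:

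- The drop-out sentence can be read as keeping withdrawn men who still supply scores. That eases the conflict, but a man lost before week 2 remains both included and excluded.
- Requiring that the drug was taken excludes almost nobody, since randomisation and injection share one half-hour slot.
- The protocol plans to collect reasons for missing scores, to judge the missing-at-random assumption.
- The SAP's first secondary analysis already models the composite using all observed scores.

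A reader might infer that a complete-case t-test is always invalid under missing at random. It is not: random loss left it unbiased, and so did equal dependence in both arms under the null.

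**Conclusion.** The point holds as a defect of wording with a possible cost in bias. As it stands, the text removes men with an observed primary outcome from the primary test for a later missed visit, contradicts the intention-to-treat statements, and leaves two population definitions in place.

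The size rests wholly on assumed loss. At 15% per arm and a true effect of -2, placebo-only dependence of 0.5 per point gives an estimate of about -1.6 and power of 0.47 instead of 0.74. Null rejection is about 6% against 2.94%, or about 16% with opposite dependence in the two arms. Random loss costs some power at this effect size but no bias. At the planned 5-point difference, power hardly moves.

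Two stronger conclusions are tempting. One is that the primary result is in fact biased: the documents give no loss rate or pattern, and the rule may have been meant for two visits only. The other is that the t-test must give way to a longitudinal model: clarifying the rule is enough, and the SAP already fits such a model. Severity: should-fix.

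**What to change.** 1. In protocol section 12, replace the exclusion sentence, and repeat the replacement in the SAP: *all randomised patients with a baseline and two-week score are analysed in their assigned arm; a missing ten-week score does not remove a patient from the two-week analysis.*
2. Make the analysis population in the same section agree with this, or label the treated full-responder set as per-protocol.
3. Keep the t-test as primary. Name the two-week contrast from the SAP's existing random-intercept model, fitted to all observed scores, as the missing-at-random sensitivity analysis. It is valid under that assumption if the model is correctly specified, and it also uses the baseline scores of men lost before week 2.

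The cost is a few sentences in the protocol and SAP, settled before unblinding. No new data or new model are needed.
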